### Interventions

5.3

None.

### Outcomes

5.4

The clinical performance of the NGS-based diagnostic approach in young children (newborns [d0–d28], infants [d29 to <1 yr], and toddlers [1 yr to <5 yr]) with severe sepsis or septic shock will be evaluated by a panel of 3 independent experts, who are not associated with the study site. The specialists will retrospectively interpret each case and evaluate whether the knowledge of NGS results might potentially have changed the respective treatment strategy. For this purpose, the members of the panel will receive clinical case summaries including NGS results and standard-of-care results from all samples tested. Moreover, they will be provided with all results of microbiological routine diagnostics from all further specimens (e.g., body fluid, tissue, bronchoalveolar lavage fluid [BALF], and endotracheal aspirate) that they, as treating physicians, would have had available in the 72 hour period before and after the NGS diagnosis. To identify potential changes in the antimicrobial management of patients that may have occurred if the results from the NGS-based technology had been available for clinical use, the panel will be provided with a special questionnaire, which has been adapted from the previously published Next GeneSiS-Trial.^[22]^

A secondary subgroup analysis is aimed to evaluate the clinical value of the use of NGS-based diagnostics for children suffering from a failure of empiric treatment within the first 3 days after sepsis onset (as assessed by death of the child or a lack of improvement of the child's clinical condition [in terms of an inadequate decrease of the age-adapted SOFA-score^[25]^] or persistently high procalcitonin levels).

### Description of analysis techniques

5.5

Standard-of-care microbiological analyses: microbiological testing of potential pathogens in the different specimens will be performed according to the usual standard operating procedures of the respective participating institution.

Here, we exemplify briefly the blood culture testing at Heidelberg University Hospital which has been described in detail elsewhere^[27]^:

After the sterile collection of 0.5 to 10 mL whole blood, it is injected into an aerobic (and if possible half of it in an anaerobic) blood culture bottle (BACTEC PLUS, BD Biosciences, Heidelberg, Germany). In cases in which it is not possible to collect a sufficient amount of blood, only one aerobic blood culture bottle is inoculated. The blood culture bottles are then incubated for at least 5 days (BACTEC, BD Biosciences). Positive cultures are analyzed using VITEK2 (Biomerieux, Nuertingen) or MALDI TOF (Bruker, Madison, WI) and then subjected to an automated resistance test (VITEK 2). Herpes simplex-1 (HSV-1) or cytomegalovirus (CMV) DNA from plasma or tracheal secretions is identified by means of a quantitative real-time (RT) PCR.^[28]^ Wound swabs, catheter tips, and stool samples are also cultured using standardized methods.^[29,30]^

### Next-generation sequencing (NGS)

5.6

The NGS-based diagnostics in the plasma samples of the study patients is carried out as follows (subject to any further technical developments).^[20]^ After the aseptic removal of 2.7 mL EDTA blood, EDTA plasma is obtained immediately by centrifugation for 10 minutes at 2500 × *g*. The plasma is then pipetted into 0.5 mL Eppendorf or 1.5 mL DNA LoBind tubes. Then, 80 μL is pipetted into a separate 0.5 mL Eppendorf tube in order to later determine the concentration of the reactive metabolite methylglyoxal (MG) from this.^[31]^ The Eppendorf tubes are then stored at –80 °C until further processing. Sample processing should be completed no later than 2 hours after the blood sample has been taken. The sample is transported for further processing to the Fraunhofer Institute for Interfacial Engineering and Biotechnology (Fraunhofer IGB, [name]) on dry ice. Here, plasma will be centrifuged again for 10 minutes at 16,000 × *g* and 4 °C and nucleic acids will be isolated using the QIAsymphony DSP Circulating DNA Kit (Qiagen, Hilden, Germany). The isolated nucleic acids (=freely circulating DNA [cfDNA]) are then quantified using the Qubit dsDNA HS Assay Kit (Life Technologies, Carlsbad, CA). In addition, quality control is carried out using the HS NGS Fragment Analysis Kit using a Fragment Analyzer or FEMTO Pulse (Advanced Analytical Technologies Inc., Heidelberg, Germany). The so-called NGS libraries are made from 0.5 to 1 ng cfDNA using the Nextera XT Library Preparation Kit (Illumina, San Diego, CA) or NEXTflex Cell Free DNA-Seq Kit (Bioo Scientific, Austin, TX) and then sequenced on a HiSeq2500 (Illumina, San Diego, CA). In the next step, human cfDNA is identified using NextGenMap. Reads mapping to the human reference genome (hg19, minimum identity between read and reference genome of 80%) and reads with low complexity (consecutive stretches of di- and trinucleotides along the whole read sequence) are excluded from further analysis.^[32]^ Finally, reads are assigned to systematic classification using the RefSeq database (release version 68; comprising 35,749 bacterial and 4340 viral genomes complemented by 12 selected fungal genomes) using the Kraken Taxonomic Sequence Classification System (Center for Computational Biology, Johns Hopkins University, Baltimore, MD).^[33,34]^ To quantify the respective reads, read counts are normalized to the corresponding library size. Of note, *Xanthomonas* species are excluded from further analyzes as they are well-known contaminants.^[35]^

### Sepsis indicating quantifier (SIQ)-score

5.7

The quantity of different species in microbiological samples will be assessed using the sepsis indicating quantifier (SIQ)-score.^[20]^ To calculate the SIQ-score, it is necessary to use the n × (*s* + 1) dimensional count matrix *D*, in which n is the number of control samples and *s* the number of species detected in all samples. Thus, *D*_*ij*_ defines the number of reads found in control sample *i* for species *j*. *D*_*i*,(*s* + 1)_ defines the number of reads that cannot be assigned to any species,^[22]^ whereby *D*_*i*,(*s* + 1)_ is usually much larger than the *D*_*ijs*_. Therefore, the probability of pathogen type *j* being in a control sample can be estimated using Equation (1):

(1)$${\hat{p}}_{j}=\frac{\sum_{k=1}^{n}D_{k,j}}{\sum_{k=1}^{n}D_{k,s+1}},j=1,...,s+1$$

As the concentration of bacteria, fungi, or viruses is usually low, Poisson distribution (Equation (2) for read counts of species *j*) is assumed.

(2)$$\lambda_{j}=\frac{\sum_{k=1}^{n}D_{k,j}}{\text{n}}.$$

To verify this assumption for each species, a standard chi-squared goodness of fit test is performed.^[22]^ The vector *C* = (*C*_1_, …, *C*_s_, *C*_s + 1_) results for reads in the analyzed patient plasma samples. Assuming a Poisson distribution with the species-specific parameter *λ*_*j*_, the *P*-value for at least *C*_*j*_ hits in a patient sample can be calculated according to Eq. (3).

(3)$$P(X\geq C_{j}\text{|}\lambda_{j})=\sum_{k\geq C_{j}}\frac{e^{-\lambda_{j}}\lambda_{j}^{k}}{k!}.$$

If this *P*-value is small, the hypothesis that “the number of hits of pathogen type *j* in the respective patient sample corresponds to the Poisson distribution found in healthy test subjects” must be rejected. It follows that the corresponding pathogen appears too often in the respective patient sample. With a defined species-specific *λ*, the “Sepsis Indicating Quantifier Score” (SIQ score) can now be derived (4) achieving a quantitative and probabilistic assessment of every detected microbe in the respective sample.

(4)$$SIQ_{j}=C_{j}*-(\text{lo}{\text{g}}_{10}[P(X\geq C_{j}\text{|}\lambda_{j})])$$

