0d to 1 wk	<100 or >180	>50	>34	<65	<36 or >38.5
1 wk to 1 mo	<100 or >180	>40	>19.5 or <5	<75	<36 or >38.5
1 mo to 1 yr	<100 or >180	>34	>17.5 or <5	<100	<36 or >38.5
2–5 yrs	>140	>22	>15.5 or <6	<94	
6–12 yrs	>130	>18	>13.5 or <4.5	<105	
13–18 yrs	>110	>14	>11.0 or <4.5	<117	
SIRS criteria in adults	>90	>20	>12.0 or <4.0	NA	<36 or >38.0

**Table 4 T4:** Overview of sepsis definitions in children and adults.

	SEPSIS-1	SEPSIS-2	SEPSIS-3	Pediatric sepsis definition
Patient group	Adults	Adults	Adults	Pediatric
Authors	Bone et al^[68]^	Levy et al^[25]^	Singer et al^[1]^	Goldstein et al^[23]^
Year of publication	1992	2003	2016	2005
Sepsis	2/4 SIRS criteria	2/4 SIRS criteria or other sepsis symptoms out of a list		SIRS criteria age-adapted
Severe sepsis	Sepsis + organ dysfunction	Sepsis + organ dysfunction	Increase in SOFA-Score ≥2 points	Sepsis + organ dysfunction
Septic shock	Sepsis + hypotonia		Sepsis + hypotonia^∗^ + serum lactate ≥2 mmol/L	Sepsis + hypotonia

In addition, a total of 60 healthy children (20 neonates [d0–d28], 20 infants [d29 to <1 yr], and 20 toddlers [1 yr to <6 yr]) will be included in the study as reference to validate a pediatric SIQ-Score (pSIQ-Score).

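### As printed, Equations 2 to 4 give an infinite or undefined SIQ score for any species with no read in the controls, so in these cases the score cannot separate a stray read from a heavy pathogen load

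*Protocol article*

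**What the plan says.** Section 5.7 gives the score in full. A count matrix is formed from n control samples and s species, where s is "the number of species detected in all samples". Equation 2 sets the species rate λ_j to the sum of control reads of species j divided by n. Equation 3 is the Poisson probability of at least C_j reads at that rate, C_j being the patient's count. Equation 4 is SIQ_j = C_j × (−log10 P). The section presents this as "achieving a quantitative and probabilistic assessment of every detected microbe in the respective sample". The Poisson form is to be checked species by species: "a standard chi-squared goodness of fit test is performed".

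The controls are described in section 5.2: "a total of 60 healthy children", 20 per age group, who "will be included in the study as reference to validate a pediatric SIQ-Score". Section 5.13 repeats the 20 per group.

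Section 5.6 lists what is removed before scoring: human reads, low-complexity reads and *Xanthomonas*. Counts are normalised to library size. Neither section states a pseudocount, a floor on λ_j, a minimum read count or a cap on the score.

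**The concern.** λ_j is a plain mean, so it is exactly zero whenever no control happens to carry a read of species j. A Poisson variable with mean zero cannot take a value of one or more, so the tail probability is zero and its logarithm does not exist. Healthy children can be expected to lack many true pathogens, and rare contaminants will often be missed in 20 or 60 controls. The formula therefore fails for both kinds of species that it is meant to tell apart.

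The score is the index test. Section 3 evaluates sequencing by means of it, and section 1 relies on it to distinguish the causative organism from contaminants. It feeds the comparison with culture (McNemar test and Cohen's κ, section 5.16) and the sequencing results put before the expert panel (section 5.4). Where the score is infinite for several species in one child, it gives no order among them.

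**Working it through.** The article states no SIQ value, so there is none to reproduce. The check evaluates Equations 2 to 4 directly.

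**Inputs from the article.** n = 20 + 20 + 20 = 60 controls (sections 5.2 and 5.13); Equations 2 to 4 (section 5.7). Section 5.7 does not say whether λ_j is pooled over ages or age-specific, so n = 20 is shown as well. The reference database holds 35,749 + 4340 + 12 = 40,101 genomes (section 5.6).

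**Step 1: no control read.** λ_j = 0/60 = 0. Every term of Equation 3 with k ≥ 1 is e^0 × 0^k / k! = 0, so P = 0 and SIQ_j = C_j × ∞. This holds for C_j = 1, 2, 5, 10, 100 and 1000 alike. Normalising to library size leaves a zero at zero. If s is read as covering only species found in the controls, λ_j is not defined and there is no score.

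**Step 2: one read among the 60 controls.** λ_j = 1/60 = 0.0167.

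| Patient reads | SIQ, λ = 0 | SIQ, λ = 1/60 |
|---|---|---|
| 1 | infinite | 1.78 |
| 10 | infinite | 243.5 |
| 100 | infinite | 33,579 |
| 1000 | infinite | 4,345,763 |

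Down the second column all counts tie. Across the columns, one read of an unseen species ranks above 1000 reads of a species seen once.

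**Step 3: how easily a species is missed in the controls.** The chance of no read in n controls is exp(−nμ) for a true background mean μ. The article gives no μ, so these are assumed values.

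| μ (reads per sample) | n = 60 | n = 20 |
|---|---|---|
| 0.001 | 94% | 98% |
| 0.01 | 55% | 82% |
| 0.05 | 5% | 37% |

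**Step 4: illustration per uninfected child.** Assume 1000 background species with a common mean μ. The expected number with an infinite score is 1000 × exp(−nμ) × (1 − exp(−μ)). For μ = 0.001, 0.01 and 0.05 this is 0.9, 5.5 and 2.4 with n = 60, and 1.0, 8.1 and 17.9 with n = 20. If the means are instead log-normal (median 0.02, log-SD 1.5), it is 3.3 and 9.8. Nearly all of these are single reads: requiring at least 2 reads cuts the log-normal figures to about 0.03 and 0.20.

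**Step 5: rules that stay finite.**
- Gamma-Poisson predictive tail: X ~ NB(0.5 + sum of control reads, n/(n+1)). With n = 60 and no control read, P(X ≥ 1) = 1 − (60/61)^0.5 = 0.0082 and SIQ = 2.1. The same formula gives 48 for 5 reads and 732 for 20.
- Pseudocount of 0.5 read: λ = 0.5/60 = 0.0083, giving SIQ 2.08 for 1 read, 273.5 for 10 and 36,589 for 100. With n = 20, λ = 0.025, giving 1.61, 225.9 and 31,819.

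Both restore an order by read count.

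**Step 6: scoring a control against itself.** Suppose one control carries the only read of a species. Scored with its own read included, λ = 1/60 and SIQ = 1.78. With that control left out, λ = 0 and Equation 4 is infinite. Scoring the controls in-sample therefore cannot reveal the failure.

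**The case against.** The strongest reply is that the article condenses a method published elsewhere. Section 5.7 takes the score and the goodness-of-fit check from cited papers, section 5.6 allows for further technical developments, and section 5.16 refers the statistics to the adult trial's publication. A zero-count rule or reporting threshold may stand there. Section 5.7 also derives the score given a defined λ. This part stands as a limit: the documents show what the printed equations do, not what the laboratory's software does. It does not remove the point, because the article prints the whole formula and claims coverage of every microbe, which the formula does not deliver.

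A second reply is that the study is exploratory, that its P-values are declared descriptive (section 5.16), and that the panel sees culture results and clinical summaries and can dismiss a single read. That is fair. Nothing in the article says that the highest score alone names the pathogen. But an exploratory study of an index test still needs the test to be defined.

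Third, the counts in step 4 rest on assumed inputs, and a simple read floor would remove most of them. That also stands, so they are illustrations only.

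A reader might also infer that one stray read outranks every genuine pathogen. The equations do not support this: a pathogen absent from the controls is infinite too, which is a tie. Only pathogens with at least one control read are outranked. Nor do the documents show that faulty control results will be reported as clean. The article plans no control positivity rate or cut-off, so step 6 matters only if one is added.

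**Conclusion.** The point holds for the equations as printed. Any species with no control read gets an infinite score or none, against the claim that every detected microbe is assessed. Among such species 1 read and 1000 reads tie, and all of them rank above any species with a control read. This is algebra and needs no assumption.

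How often it bites is not known from the article. Under the assumed fixed rates it would be about 1 to 5 species per uninfected child with 60 controls and 1 to 18 with 20, nearly all from single reads. These are not estimates for this trial.

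That λ_j is treated as known, and that the Poisson form is checked only by a chi-squared test, are secondary matters on which the conclusion does not depend.

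**What to change.** Before any patient sample is scored, replace the plug-in Poisson tail in Equation 3 by a rule that stays finite at zero control reads, and state that it applies to every species detected in a patient or a control. Either rule in step 5 will do. The predictive tail also allows for λ_j being estimated from few controls; the pseudocount is the smaller change. Apply the rule to patient and control counts on one common scale, since section 5.6 normalises reads to library size while Equation 3 is written for whole counts. If the cited method already has a zero-count rule, print it with the equations instead.

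If the controls are also used to report positivity or to set a cut-off for the paediatric score, score each control with λ_j taken from the other controls.

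The cost is one formula and, if needed, one loop in the scoring code, with no new data. The downside is somewhat lower scores and, if one is reported, a less favourable false-positive rate in the controls. For a species with one read in 60 controls, for example, the predictive tail gives P(X ≥ 1) = 1 − (60/61)^1.5 = 0.0245 and a score of 1.61 for one patient read, against 1.78 now.

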### Data collection and participant timeline

5.8

Once after enrollment, basic data will be collected and, if necessary, corrected or supplemented during the course of the study. These basic data include patient demographics (age, sex, etc), relevant underlying conditions (such as oncologic or hematologic diseases, metabolic or neurological disorders, lung or kidney dysfunction), and information on pre-existing immunosuppressive diseases or the use of immunosuppressive medication for example in the context of transplanted patients.^[36]^ Moreover, the time of admission to hospital or the intensive care unit, referrer characteristics (emergency room, operating theater, recovery room, normal ward, intermediate care station), recent medical history (preoperations, reoperations, etc), suspected or proven infectious focus, and anti-infective treatment in the days and weeks preceding to the enrolment in the study will all be recorded. In addition, at sepsis onset (=onset) and 72 hours later (=72 hours): the following parameters are recorded: procalcitonin (PCT), leukocyte count, C-reactive protein (CRP), body temperature, the need for invasive ventilation, Horowitz quotient (mm Hg), oxygenation index (OI), catecholamine requirements (noradrenaline, adrenaline, dobutamine, dopamine) (μg/kg/min), 24 hours total balance (±mL/24 h), need for renal replacement therapy, age-adapted Sequential Sepsis-related Organ Failure Assessment (SOFA) and quick (q) SOFA score,^[26]^ procedures for the diagnosis/treatment of infection, radiological testing for the diagnosis/evaluation of potential infection, indwelling vascular access devices, vital status, and the antimicrobial therapy on the intensive care unit (preparation, start, and end of the respective application). Laboratory parameters will be determined in the analysis center of the respective participating institution. Discharge data will include date of discharge (ICU and hospital), discharge destination (general hospital floor, skilled nursing facility, and home), and vital status at discharge (survival/death). The final outcome evaluation of patients will be performed at 28 days after onset. A detailed flow chart of the trial specific procedures, assessments, and visits for participants is provided in Table 5.

**Table 5 T5:** Detailed flow chart of specific procedures, assessments, and visits (Spirit figure).

Flow chart of visits	Check	Visit 1	Visit 2	Visit 3	Visit 4
Time frame		Onset		72 h	28d
Eligibility criteria	•				
Written informed consent	•				
Baseline data		•			
Clinical data		•		•	
Next generation sequencing		•		(•)	
Blood cultures		•		(•)^†^	
PCT-measurement		(•)^∗^		(•)^∗^	
Urine samples		(•)^∗^	(•)^∗^		
Outcome evaluation					•

### Data collection from reference patients

5.9

For the 60 reference patients, only basic data will be recorded. Blood samples serve as reference values.

### Microbiological diagnostics

5.10

Parallel to the collection of the basic data, at sepsis onset, 72 hours after sepsis onset and, if indicated by the treating physician, at a maximum of one further time within the first 3 days after sepsis onset, samples for NGS-based diagnosis with subsequent calculation of the SIQ score by the Fraunhofer IGB will be collected. Routine microbiological findings from other sample materials (e.g., surgical swabs, drainage secretions, tracheal secretions, tissue samples, etc) are included in the evaluation, provided that they have been preserved in a time window of 72 hours before or after plasma samples are obtained for NGS-based diagnostics.

### Sample size

5.11

For reasons of feasibility, only 150 children (50 neonates [≤28 d], 50 infants [29 d to <1 year], and 50 children up to preschool age [1 year up to the age of <5 years]) will be included in this study. Due to the exploratory nature of this trial no concrete sample size calculation has been performed. However, the Next GeneSiPS-Trial is to be seen in the context of the Next GeneSiS-Trial,^[22]^ in which a total of 500 adult patients with sepsis/septic shock are included.

### Recruitment

5.12

All neonates, infants, and toddlers up to the age of 5 years (up to the 5th birthday), who are treated on an ICU in one of the participating centers (6–10 hospitals of maximum care), who have suspected or proven severe sepsis or septic shock (according to the pediatric sepsis definition^[23]^) and whose parents or legal representatives consent to this study will be considered for study inclusion.

### Recruitment of reference patients

5.13

Children (20 newborns [≤28 d], 20 infants [29 d to <1 year], and 20 children up to preschool age [1 year up to the age of <5]) without signs of infection undergoing elective surgery under general anesthesia requiring the installation of a central venous catheter and a urine catheter will be included as reference patients.

### Data collection methods

5.14

Data collection will be carried out as described previously for the Next GeneSiS-Trial.^[22]^ All data collected in this trial will be recorded on electronic case report (eCRF) specifically adapted for the study using an electronic data capture (EDC) system (/REDCap, Vanderbilt University, Nashville, TN).^[37,38]^ The investigators are responsible for ensuring that all parts of the eCRFs are filled in correctly. The completed eCRF must be approved by the investigator or by a designated sub-investigator.

### Data management

5.15

According to §13 of the Good Clinical Practice Ordinance,^[39]^ all important trial documents (e.g., eCRFs) will be archived for at least 10 years after completion of the clinical trial.

### Statistical methods

5.16

As the Next GeneSiPS-Trial has to be understood as an extension of the Next GeneSiS-Trial, statics will be carried out as previously published.^[22]^ In brief, case by case NGS results will be compared with those obtained using standard-of-care microbiological testing. The McNemar test and Cohen *κ* statistics are used to check the agreement and concordance.^[40,41]^ All percentages and confidence intervals (Cis) are calculated using exact methods and rounded accordingly. The clinical value of NGS-based diagnostics is determined as follows: 3 independent experts (not associated with the study site) compare the results obtained using NGS-based diagnostics with those of routine microbiological diagnostics and evaluate the findings using a special questionnaire with regard to their relevance for the anti-infective therapy strategy. The evaluation of the questionnaire is carried out according to the majority rule. Further subgroup analyses will focus on patients in whom the anti-infective therapy did not work sufficiently, that is, in whom organ dysfunction did not improve or who have died (Chi-squared test for categorical data and further methods of variance analysis for continuous data). The statistical evaluation is carried out by means of SAS (SAS Institute, Cary, NC). Detailed descriptive statistics will be provided for all data collected. The chi-square test will be used for evaluating categorical variables and *t* tests will be used for evaluating continuous data univariably. Appropriate regression methods will be used for multivariable analyses. A *P*-value of <.05 is assumed to be statistically significant. However, given that the Next GeneSiPS-Trial is a not statistically powered study of exploratory nature, these values are only of descriptive value.

